## Abstract

**Background:**

Long-term studies of smokers who switch to lower nicotine yield cigarettes have been identified by the World Health Organization Study Group TobReg and the US Food and Drug Administration as one key area where new knowledge is required to guide science based regulation. The limited number of long-term switching studies have concluded that smokers who switch to lower nicotine yield cigarettes show evidence of partial compensation. Since the European Union tobacco product directive of 2001 introduced tar and nicotine yield ceilings, there has been no long-term observational switching study. To address the limitations of previous studies where smokers were forced switched for relatively short durations, we plan to undertake a long-term study of spontaneous switching which is appropriately powered and includes non-switchers as a control group.

**Methods/design:**

Healthy adult smokers aged 21–64 years will be enrolled into this 5-year non-residential, multicentre study across 10 cities in Germany. They will be assessed at 10 timepoints with 6 month intervals during which inclusion criteria will be reassessed and spent cigarette filter tips, saliva and 24 h urine samples will be collected. These samples will be used to determine average daily cigarette consumption, estimate mouth-level exposure to tar and nicotine and measure selected biomarkers of exposure, respectively. Spontaneous changes in subjects’ preferred cigarette products and any consequent change in tar or nicotine yield will be monitored. Subjects will be required to complete questionnaires on quality of life, smoking behaviours, smoking-related sensory attributes and recent life changes.

**Discussion:**

The planned study is anticipated to contribute to understanding smokers’ behaviours and their consequent exposure to smoke constituents. It will also allow assessment of compensatory changes in their behaviour following spontaneous switching of cigarette product smoked. Data from this study are expected to provide insights into study design and conduct for non-clinical assessment of smokers’ exposure as part of post marketing surveillance programmes.

**Trial registration:**

Current Controlled Trials Database reference ISRCTN95019245.

## Background

The long-term risks associated with cigarette smoking, particularly cancer [1,2], cardiovascular disease [3] and chronic obstructive pulmonary disease [4], are well established. Few longitudinal studies, however, have assessed spontaneous changes in smoking behaviour, and especially whether a smoker’s nicotine uptake remains constant or changes over time. Studies in adult smokers have shown stable values for cigarette consumption and concentrations of carboxyhaemoglobin (a biomarker for exposure to carbon monoxide) over periods of several months when smoking the same product [5-7].

### Previous longitudinal studies of spontaneous product switching

A small number of longitudinal studies have investigated the effects of spontaneous product switching on smoking behaviour [8-12] and the extent of compensatory smoking behaviour. Compensation occurs when a smoker changes their smoking behaviour in some way, for example, puff volume, frequency or the number of cigarettes smoked, in response to smoking a cigarette of higher or lower smoke yield. Complete compensation occurs when a smoker maintains their intake following a change, no compensation results in a change that is proportional to the change in product yield, and incomplete compensation describes changes between these two extremes [13]. In a study in the USA, conducted by the American Cancer Society between 1959 and 1972 on changes in cigarette consumption in relation to changes in tar and nicotine yield, data from 28,561 male smokers were reported [8]. By the end of the study, 16,991 (59%) smokers had changed to cigarettes with lower tar and nicotine yields than at the start of the study, 8,190 (29%) had not changed, and 3,380 (12%) had changed to cigarettes with higher yields. Among smokers who had switched to cigarettes with increased tar and nicotine yields, 29% had also increased the number of cigarettes they smoked per day, while 39% had decreased the number smoked. Likewise, although 32% of smokers who had switched to lower tar and nicotine products smoked more cigarettes per day, 34% smoked fewer. The data suggest that changes in cigarette consumption were not related to smokers changing to cigarettes of higher or lower tar and nicotine yields, though the yields of tar and nicotine in the cigarettes smoked during this period would have been significantly higher than those typically seen today in most countries.

The effects of changing to lower tar yield cigarettes was investigated over a period of 13 years (1971–1984) in nearly 600 male smokers [9]. Average cigarette consumption reduced over the study period, but to a lesser extent in smokers who had changed to lower tar cigarettes than in those who had not. At the 1984 follow-up, similar amounts of urinary nicotine metabolites were excreted by smokers who had and had not changed to lower tar cigarettes at data collection, which suggests compensatory smoking behaviour following switching. In a study of the effects of spontaneous switching on nicotine and carbon monoxide exposure in 203 smokers, a reduction in cigarette consumption of 6.6 cigarettes per day was observed in smokers who changed spontaneously to lower nicotine yield cigarettes, with smaller reductions in consumption for smokers who had not changed product or who had changed to higher nicotine yield cigarettes (1.9 and 1.8 fewer cigarettes, respectively) [10]. For the smokers who changed to lower nicotine yield cigarettes, absolute plasma cotinine levels were reduced, however, plasma cotinine levels per cigarette were little altered, which suggests an increase in smoking intensity. In a longitudinal study in South Germany, 41 smokers changed their cigarette during the study, 13 of whom changed to a lower tar product [11]. The extent of the reductions in cotinine concentrations suggested 55% compensation.

In 2002–2005, Muhammad-Kah and colleagues assessed spontaneous product switching in 2,542 smokers in the USA, of whom 68 switched to higher tar products and 23 switched to lower tar products, with subsequent decreases of two cigarettes and increases of two cigarettes per day, respectively [12]. Substantial variability and insufficient power to detect significant differences in biomarkers of exposure, however, led to no definitive conclusions being reported.

Since 2004, in the European Union the maximum permitted tar and nicotine yields have been 10 mg and 1 mg per cigarette, respectively, measured using International Organization for Standardization (ISO) methods [14]. Following the introduction of these regulations, long-term changes in consumption [15], nicotine uptake, exposure to smoke toxicants and the effects of switching to cigarettes of lower yields are unclear. The World Health Organization (WHO) Study Group on Tobacco Product Regulation (TobReg) identified a number of research areas as being key to enhancing this knowledge [16], which include assessment of whether an increase or decrease in nicotine content per unit (e.g. per cigarette) would be beneficial to a population’s health and investigation of contents and design features that might reduce toxicity, consumer appeal and/or the potential for dependency. In 2009, the US Food and Drug Administration was given jurisdiction over tobacco products via the US Family Smoking Prevention and Tobacco Control Act, and in 2012 issued draft guidance on the key areas to be investigated in making marketing applications for modified-risk tobacco products, which includes the requirement for post-market surveillance studies [17]. The FDA is also considering product standards, which could involve the limiting of harmful and potentially harmful constituents and nicotine.

### Study objectives

We plan to undertake a longitudinal study to address some of the TobReg research aims [16], to provide insights into appropriate study designs for undertaking post marketing surveillance programmes. We will study the effects of spontaneous product switching over a 5 year period on the following features of smoking behaviour: average daily cigarette consumption, mouth-level exposure (MLE) to nicotine and tar [18]; uptake of nicotine, assessed by measurement of urinary and salivary biomarkers of exposure; and exposure to the smoke toxicant 4-(methylnitrosamino)-1-(3-pyridyl)-1-butanone ([NNK] a tobacco-specific nitrosamine) through the measurement of metabolites in urine. Secondary objectives are to assess any compensatory smoking behaviour and changes in quality of life and sensory perception following spontaneous product switching.

## Methods/design

### Study design

The study will be performed in Germany over 5 years and will involve 10 non-residential study centres. The study will comprise 10 timepoints over the 5-year period, each of 6 months’ duration. Each timepoint will include a 12-day fieldwork period consisting of three clinical visits separated by ambulatory periods (Figure 1, Table 1) and telephone based interviews between the fieldwork periods.

**Figure 1 F1:**
[figure not shown]
Study activities during fieldwork periods.

**Table 1 T1:** Study activities per timepoint

	**Day 1 Visit 1**	**Days 2 to 8**	**Day 9 Visit 2**	**Day 10**	**Day 11**	**Day 12 Visit 3**	**Call 1**	**Call 2**	**Call 3**
Informed consent^a^	X								
Demographic data (height^b^ and weight)	X								
Medical history	X								
ECG^b^	X								
Spirometry (FEV_1_)	X								
Blood pressure	X								
Inclusion/exclusion criteria	X								
**Materials provided to Subject**									
Urine collection bottles			X						
Aluminium containers for butt collection	X		X						
Issue of cigarettes for 1 day			X						
Filter cutters with integrated tin			X						
Sensory questionnaire			X						
**Subject activities**									
Usual subject environment		X		X	X		X	X	X
Smoke own supply of cigarettes	X	X	X	X		X	X	X	X
Collection of cigarette butts		X	X	X					
Collection of part-filter tips					X				
Start 24 hour urine collection					X				
End 24 hour urine collection						X			
Smoke provided cigarettes					X				
Complete questionnaires	X		X		X	X			
Telephone interview				X			X	X	X
**Provided by Subject**									
Butts			X			X			
Urine						X			
Sensory questionnaire						X			
Filter tip						X			
Saliva						X			

^a^Informed Consent will be taken at visit 1, first fieldwork period only or if updated.

^b^Height and ECG will be measured at visit 1, first fieldwork period only.

The protocol and the informed consent form have been reviewed and approved by the Ethics Committee of the Bavarian State of Chamber of Physicians (Ethik-kommission der Bayerischen Landesärztekammer), Munich, Germany (Ethics Committee Number 08036) as the central voting ethics committee for the study. Approval was given by all local ethics committees relevant to the site investigators (Sächsische Landesärztekammer, Ärztekammer Nordrhein, Landesärztekammer Baden-Württemburg, Ärztekammer Hamburg, Ärztekammer Berlin). The principal investigator or designated investigators will ensure that subjects are provided with oral and written information regarding the study, associated activities and storage of data and samples. Subjects will be required to read, sign and date informed consent forms before enrolment in the study. The study will be conducted by an independent contract research organisation (CRO), Harrison Clinical Research Deutschland GmbH, Munich, Germany, in accordance with the ethics principles of the Declaration of Helsinki [19] and the International Conference on Harmonisation Guidelines for Good Clinical Practice [20]. Subjects will be compensated for the inconvenience and effort in participation in the study, at rates approved by the ethics committee of Bayerischen Landesärztekammer.

### Study population

#### Identification of subjects

Male and female adult smokers of Lucky Strike Red King Size cigarettes (LSR) (ISO yields 10 mg tar/cigarette and 0.8 mg nicotine/cigarette) will be eligible. Recruitment of subjects will be undertaken by a market research agency (MRA), Ipsos Operations GmbH, Hamburg, Germany. Potential subjects will be selected from people approached in the streets in the vicinity of shops selling tobacco products (kiosks, newsagents, grocers etc.) and those who respond to local newspaper advertisements.

#### Inclusion criteria

Subjects will be required to satisfy the following inclusion criteria: age 21–64 years at the time of signing the informed consent; female subjects must not be pregnant or lactating at the time of enrolment; be in good health, as determined by medical history, baseline 12-lead electrocardiography (ECG), lung-function tests and measurement of blood pressure; smoke eight or more LSR cigarettes per day and have done so for at least 6 months at the time of enrolment; willingness to provide written informed consent to participate in the study; and willingness to purchase cigarettes for personal use. Continued eligibility for inclusion according to these criteria will be reassessed at each timepoint during the study.

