Study staff will also contact participants by telephone four times during each timepoint, at approximately 2 and 4 months after the last fieldwork visit (calls 1 and 2), 1 week before the next fieldwork period (call 3) and on day 10 of fieldwork periods (call 4). During telephone contact, the following activities will take place: calls 1 and 2 will be interviews with subjects to verify they still meet the original non-medical inclusion criteria and to record which cigarette products are currently being smoked, reasons for any change in current cigarette product smoked since the previous timepoint and self-reported daily consumption; call 3 will be to remind subjects of their visit 1 appointment and determine whether they have changed their cigarette product; call 4 will be to remind subjects to collect part-filter tips and urine on day 11.

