#### Monitoring of changes in cigarette consumption

Checks on whether each smoker has changed their main cigarette product will be carried out at calls 1, 2 and 3 of each timepoint. The products reported by the subjects during call 2 will be obtained by the sponsor for supply at the next fieldwork period. Call 3 will identify any changes in a subject’s cigarette product smoked, one week before the fieldwork period. Change to cigarettes with a lower ISO tar yield compared to those smoked at baseline (e.g. from 10 mg to 6 mg), a higher ISO tar yield (e.g. from 6 mg to 10 mg) and to a different cigarette with the same ISO tar yield (e.g. one 10 mg ISO tar product to another 10 mg ISO tar product) will be permitted. Subjects will be considered no longer eligible if they change their smoking habits in any of the following ways: change to smoking cigarettes that are not TVO compliant; change to smoking non-filtered products; change to smoking self-rolled (roll your own) cigarettes or self-filled “stix” (make your own) cigarettes, with or without filters; change to using chewing tobacco or other smokeless tobacco products; and use of nicotine-replacement therapy or decision to quit smoking.

The MRA will maintain all information regarding switches in products and smoking behaviour.

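### Re-applying the inclusion criteria after enrolment, including at least eight LSR cigarettes per day, contradicts the rule that permits product switching and, if only the number is kept, makes follow-up depend on the consumption outcome

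*Protocol article*

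**What the plan says.** The section Inclusion criteria requires subjects to "smoke eight or more LSR cigarettes per day and have done so for at least 6 months at the time of enrolment". It closes with "Continued eligibility for inclusion according to these criteria will be reassessed at each timepoint during the study". LSR is one named product with ISO yields of 10 mg tar and 0.8 mg nicotine (Identification of subjects).

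The section Fieldwork periods repeats the re-check. Calls 1 and 2 are interviews "to verify they still meet the original non-medical inclusion criteria", and they also record the current product, the reasons for any change and self-reported daily consumption.

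The section Monitoring of changes in cigarette consumption gives a different rule. "Change to cigarettes with a lower ISO tar yield compared to those smoked at baseline" is permitted, as are changes to a higher or the same tar yield. A separate list follows, introduced by "Subjects will be considered no longer eligible if they change their smoking habits in any of the following ways". It covers non-compliant, non-filtered, self-made and smokeless products, nicotine replacement and quitting. Neither leaving LSR nor smoking fewer than eight a day is on it.

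Sample size and power calculations and Statistical analysis are built on non-switchers, down-switchers and side-switchers, with at least 51 subjects sought in each. The analysis uses the per protocol population.

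**The concern.** A subject who changes product no longer smokes eight LSR a day, so the re-check and the monitoring rule cannot both be followed. Sites and the market research agency have to choose, and the article does not say which part of the entry criterion lapses.

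The natural repair is to ignore the brand and keep the number. That carries its own problem. Average daily consumption is the first feature named in Study objectives, and daily mouth-level exposure is the per-cigarette value multiplied by the cigarettes smoked on day 11 (Smoking and part-filter collection). A floor of eight would keep or remove subjects according to the value of an outcome. Data not collected after removal cannot be recovered by a later analysis plan.

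**Working it through.** **The plan's own figure.** 1000 × (1 − 0.204)^5 = 319.6, which agrees with the stated 319 completers. The point does not rest on an arithmetic error.

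**Reading 1: the criterion re-applied as written.** It requires eight or more LSR a day. A down-switcher or side-switcher has left LSR and fails. Eligible switchers: 0 in each group, against 51 sought. This conflicts with the monitoring section and with the group structure of the sample size and model.

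**What calls 1 and 2 can check.** The non-medical inclusion criteria are age (fixed at signing), the smoking criterion, and willingness to consent and to buy cigarettes. The smoking criterion is the only one about smoking, and product and consumption are exactly what these calls record. The re-check therefore has a concrete target.

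**Reading 2: brand dropped, floor of eight kept.** The Background cites one spontaneous-switching study in which "a reduction in cigarette consumption of 6.6 cigarettes per day was observed in smokers who changed spontaneously to lower nicotine yield cigarettes"; the fall in non-switchers was 1.9. With these average falls, a down-switcher starting below 8 + 6.6 = 14.6 a day drops under eight, and so does a non-switcher starting below 8 + 1.9 = 9.9. Another cited study found a rise of two a day in those who moved to lower tar.

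A simulation shows the possible size. Assumptions, none given in the article: normal baseline with mean/SD 14/5, 16/6, 18/6 or 20/7, truncated at eight (means after truncation about 15 to 21); the same baseline in both groups; normal change with SD 4; subjects below eight removed. Non-switchers change by −1.9 throughout.

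| Baseline mean/SD | Non-switchers removed | Down-switchers removed, change −6.6 | Retained difference (true −4.7) | Down-switchers removed, change +2 | Retained difference (true +3.9) |
|---|---|---|---|---|---|
| 14/5 | 19% | 48% | −3.6 | 5% | +3.3 |
| 16/6 | 13% | 37% | −3.9 | 3–4% | +3.5 |
| 18/6 | 10% | 29% | −4.1 | 2% | +3.6 |
| 20/7 | 7% | 22% | −4.2 | 2% | +3.7 |

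True differences: −6.6 − (−1.9) = −4.7 and 2 − (−1.9) = +3.9. Attenuation, 1 − retained/true on unrounded values, is 10% to 24% with −6.6 and 6% to 16% with +2. The difference moves toward zero in both cases; the group that loses more subjects reverses.

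**The case against.** The strongest reply is that the article shows what it means. The monitoring section is the specific on-study rule and permits switching. Day-11 cigarettes are matched to each smoker's current product. The calls that re-check criteria also ask why the product changed. Sample size and model both need switchers. A reader might infer that the study plans to drop every switcher; the documents do not support that. This part is a contradiction in wording.

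Second, the phrase about the time of enrolment in "smoke eight or more LSR cigarettes per day and have done so for at least 6 months at the time of enrolment" can be read as tying the whole criterion to entry. The timepoint re-check would still have content, because medical history, blood pressure and spirometry are repeated. This reading is possible, but a call made to "verify they still meet the original non-medical inclusion criteria" points the other way, and nothing in the article settles it.

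Third, nowhere is a fall below eight a day said to lead to withdrawal. Subject withdrawals names the subject's own choice, suspected protocol violation and loss to follow-up. That stands: the selection problem arises only if the floor is enforced.

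Fourth, a reader might infer that down-switchers would be removed most often. That rests on the single 203-smoker study. Elsewhere in the Background, consumption fell less in those who moved to lower tar than in those who did not, or rose by two a day, or showed no relation to the change in yield. Differential loss of down-switchers is therefore not established.

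**Conclusion.** The contradiction is real and stands in the text: two sections re-apply a criterion that a third section and the whole group structure set aside. It needs correcting because it governs who remains in a five-year cohort.

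The selection effect is conditional. If the floor of eight is enforced with the brand ignored, group differences in change of consumption shrink by about 6% to 24%. That range depends on the assumed baselines of 15 to 21 per day, a change SD of 4 and equal baselines across groups. The pull toward zero appears with both cited directions of change; the size, and which group loses more, are not fixed by the documents.

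**What to change.** Reconcile Inclusion criteria and Fieldwork periods with the monitoring section. State that the smoking criterion (LSR, at least eight per day) applies at enrolment only, and that subjects who switch product or fall below eight a day stay in follow-up and in the analysis population. Reword the purpose of calls 1 and 2 to match.

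Leave three things unchanged: re-assessment of the health criteria, re-assessment of the exclusion criteria at each timepoint, and the monitoring section's list of disqualifying changes. Cutting later checks back to that list alone would go too far, because the health criteria and most of the exclusion criteria are not on it.

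The cost is a short clarification of the text and of the call script. It needs no extra recruits or procedures.

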#### Exclusion criteria

Subjects who fulfil any of the following criteria will not be enrolled: having an existing chronic disease, such as asthma, cardiovascular disease, chronic obstructive pulmonary disease, or a history of lung cancer or any other tobacco-related disease, as determined by the principal investigator and/or site investigator; participation in another study of smoking habits in the previous 6 months; trying to stop smoking or considering doing so in the next 2 months; a candidate or an immediate family member working in public relations or advertising for the tobacco industry, including the sale or manufacture of tobacco goods; consumption of tobacco products other than factory-made cigarettes available on the German market (e.g. products that do not comply with the German Tobacco Ordinance Act, Tabakverordnung [TVO], smokeless tobacco products, and non-filtered products such as cigars or pipes); and candidates who in the opinion of the principal investigator and/or site investigator should not participate in the study. These exclusion criteria will be reassessed at each timepoint.

